### Follow-up and outcome evaluation

Clinical assessments are performed at enrollment; at 24 h after the onset of symptoms; on the 10th day after admission; and on the 90th day after the stroke. During the follow-up period, the following scales will used:the GCS assessing the level of consciousness according to the score ranging from 15 (normal) to 3 (deep coma);the NIHSS measuring neurologic deficit according to the score ranging from 0 (normal) to 42 (coma with quadriplegia), the mRS evaluating functional independence, the BI assessing the ability of daily life. More detailed information about the schedule of study visits is shown in Table 3.

**Table 3 Tab3:** Study visits

Assessment method	Screening	Onset (0 h)	24 h	10–14 days	90-day follow-up
Patient population	W	–	–	–	–
History	W	–	–	–	–
Physical examination	W	W	–	–	–
CT/CTA	W		W	W	–
Confirmation of entry criteria	W	–	–	–	–
Signing consent form	W	–	–	–	–
Serum and urine test	W	–	–	–	–
Concomitant medication or treatment	W	W	W	W	W
GCS	W	W	W	W	–
NIHSS	W	W	W	W	W
BI	W		–	W	W
mRS	–	–	–	W	W
Adverse events	w	w	w	w	W
Summary of patient	–	–	–	–	W

*CT* computed tomography, *CTA* computed tomography angiography, *NIHSS* National Institutes of Health Stroke Scale, *mRS* modified Rankin Scale, *BI* Barthel Index, *GCS* Glasgow Coma Scale

### Adverse event validation

All adverse events will be recorded during the stay in hospital and all serious adverse events will be recorded 90 days after onset. Clinical events committee, which are composed of four expert physicians independent of the research centers, will validate all adverse events. Relatedness categories are as follows: (1) primary disease-related: events obviously due to primary disease with no time relationship to the therapy, or medication. (2) concomitant disease-related: events due to diseases instead of the primary disease with no time relationship to therapy or medication; (3) TCM medicine-related: events obviously due to TCM medicine with no time relationship to other therapy;(4) medicine unknown: medicine related but unable to attribute a specific medicine; (5) individual difference-related: events have strong time relationship to individual constitution, whose allergic constitution are intolerant to traditional Chinese medicine (TCM); (6) other; and (7) unknown.

### Primary outcome

The primary end-point measure is the percent change in the hematoma volume measured by ABC/2 Coniglobus formula (Kothari et al. 1996) at the 24th hour after the onset. Hematoma growth is operationally defined as an increase in the hematoma volume of >33 % as measured by image analysis on the 24 h CT compared with the baseline CT scan.

### Secondary outcomes

Three secondary clinical efficacy outcomes are included as follows: (1) death owing to any cause on the 14th day; (2) disability as defined by mRS score ≤2 on the 90th day; and (3) change in NIHSS score at the 24th hour after the onset of symptoms.

In the study two technical efficacy outcomes are included as follows: (1) volume of hematoma growth as measured by a CT scan at 24 ± 3 h after onset of symptoms compared with the baseline CT scan; (2) recurrent bleeding measured by CT scan on 10 days after drug administration.

Two study safety outcomes are included as follows: (1) all serious adverse events; (2)hematoma growth at 24 ± 3 h.

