## Background

HICH is one of the most devastating forms of stroke which is a main cause of death and disability around the world (Roach et al. 2005), playing a significant part in morbidity and mortality worldwide (Qureshi et al. 2009). The proportion of patients with ICH who died within 30 days has risen to nearly 40 %, and most of the survivors cannot make a full recovery (Qureshi et al. 2009; van Asch et al. 2010). Approximately two-third of ICH patients suffer hematoma enlargement within 24 h of ictus (Lim et al. 2008). Moreover, hematoma growth is an independent prognostic determinant (Davis et al. 2006). Several reasons may be related to the hematoma enlargement in the early stage of ICH, including high blood pressure, “spot” sign of CT scan, sex, age, time window, anticoagulation drugs (Lim et al. 2008). But so far there have not been specific therapies or treatments preventing hematoma expansion and improve the outcome after ICH. Furthermore, it has been confirmed that neither mini-traumatic operation nor the present accessible medicine is proved to be the ideal treatment based on the available evidence-based medical researches (Morgenstern et al. 2010; Mendelow et al. 2013; Mayer et al. 2008).

Faced with the limitations of the current available therapies, herbal medicine of promoting blood circulation (PBC) and removing blood stasis (RBS) are widely and efficiently used in Chinese hospitals to treat HICH based on the TCM theory of ‘the blood flow outside the vessels is the blood stasis’. However, whether these herbal medicine can cause hematoma enlargement leading to serious adverse events is undefined until now (Li et al. 2015).

In order to evaluate the safety of PBC and RBS herbal drugs, we design a prospective, randomized, open, double-blind controlled clinical trial on the hematoma enlargement in HICH patients treating with PBC and RBS herbal medicine within 6 h time window from the symptom onset.

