### CT scanning

At screening, the baseline CT scans are obtained immediately after arriving at treating hospital to identify intracerebral hemorrhage; the first follow-up CT scans are done at 24 h after the onset of symptoms (range 21–27) to assess hematoma growth; and the second follow-up CT scans are performed on 10 days (range 8–14) after drug administration. The hematoma volume is measured by ABC/2 Coniglobus formula (Kothari et al. 1996). Hematoma growth is operationally defined as an increase in the hematoma volume of >33 % as measured by image analysis on the 24 h CT in comparison with the baseline CT scan (Kothari et al. 1996) (if the first follow-up CT scan cannot be done within 24 h from the onset, a 48-h CT scan will be analyzed). Blinding for the two neuroradiologists is maintained through analyzation of digital CT data. Computerized planimetric techniques are used to calculate the hematoma volume to valuated the primary end point. In a previous study, the interobserver agreement of this method has been proven perfect (Xu et al. 2015).

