### Statistical analyses

All analysis are by intention to treat with a beta level of 0.10 and an alpha level of 0.025 (Type I and Type II error). The primary outcome is the percent change in the volume of the hematoma measured by a CT scan at 24 ± 3 h after the onset compared with the baseline CT scan. The volumes of the hematoma measured by a CT scan will be analyzed using generalized linear mixed models. The subjects and the readers (two neuroradiologists) will be defined as random effects, and the baseline volume of hematoma, the time from the onset to CT scanning, and the time from CT scanning to study intervention will be defined as fixed-effect covariates. The percentages of changes in the volume of hematoma are transformed to normality and eliminate negative values via logarithmic transformations. Comparisons will be made between the two treatment groups with placebo using Bonferroni’s method with a threshold of significance of 0.0167. The threshold of significance for all other comparisons was 0.05. Subjects died before finishing the follow up will be assigned the worst possible scores for measures of neurologic deficit and function prognosis. Regarding surviving subjects with missing outcome data, the last visit will be carried down. The scores on mRS will be analyzed in a cumulative logit model, with statistical adjustment for age, the baseline hematoma volume, the site of hemorrhage, and the baseline neurological status. The scores on the BI and NIHSS will be analyzed with Wilcoxon rank-sum tests. The difference of the frequency of SAE in the three groups at 3 months will be analyzed with Fisher’s exact test or the Chi square test. All dates will be analyzed via SPSS software, version 21.0.

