### Lost-to-follow-up and missing data

It is supposed that there is no missing safety data on SAE, because of the careful observation and detailed records while in hospital. For surviving patients with missing outcome data, the last observation was carried forward. Regarding other incomplete primary outcome data, we will use multiple imputation to fill in missing data with standard statistical procedure.

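### Recurrent bleeding is scored on the day-10 CT and no rule gives a value to patients who die before it, so fatal rebleeds are not counted as recurrent bleeding in any arm

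*Protocol article*

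**What the plan says.** Under Secondary outcomes, the second technical efficacy outcome is "recurrent bleeding measured by CT scan on 10 days after drug administration". The CT scanning section states that "the second follow-up CT scans are performed on 10 days" after drug administration, with a range of 8 to 14 days. The only other scheduled scan after baseline has a different purpose: "the first follow-up CT scans are done at 24 h after the onset of symptoms" (range 21 to 27 h), to assess hematoma growth.

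Three rules deal with deaths and missing data:

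- **Deaths** (Statistical analyses): "Subjects died before finishing the follow up will be assigned the worst possible scores for measures of neurologic deficit and function prognosis".
- **Survivors** (Statistical analyses): "Regarding surviving subjects with missing outcome data, the last visit will be carried down". Lost-to-follow-up and missing data repeats this: "For surviving patients with missing outcome data, the last observation was carried forward".
- **Imputation** (Lost-to-follow-up and missing data): "Regarding other incomplete primary outcome data, we will use multiple imputation to fill in missing data with standard statistical procedure".

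On expected mortality, the Background says "The proportion of patients with ICH who died within 30 days has risen to nearly 40" per cent.

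**The concern.** Each of the three rules has a stated scope, and recurrent bleeding in a patient who dies before the day-10 scan falls outside all of them. Followed as written, the outcome has a value only for patients who live to be scanned, and survival to the scan is something that a rebleed can itself change.

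This matters because the section justifying the three groups names rebleeding as the risk of stasis-breaking herbs and says that leech can cause it. Table 2 lists Hirudo in the RBS arm. Treatment lasts 10 days, so most of the exposure comes after the 24-h CT, and this is the one named bleeding outcome for that period. If severe rebleeds leave both numerator and denominator, a real absolute excess in a herbal arm would look smaller and be harder to detect.

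**Working it through.** The article states no figure for this outcome, so there is none to reproduce. The check has a textual part and an illustration.

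**Text.** For a patient who dies between the 24-h CT and the day-10 CT:

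- Worst score does not apply: recurrent bleeding is not a deficit or function score.
- Carry-forward does not apply: the patient is not a survivor.
- Multiple imputation does not apply: this is not the primary outcome.

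**Illustration.** From the article: 360 patients allocated 1:1:1, so 120 per arm, and a threshold of 0.05 for comparisons other than the primary ones. Assumed, because the article gives no rates:

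- r, true risk of rebleeding: 5% on placebo, 10% or 15% on a herbal arm
- f, share of rebleeders who die before the scan: 40% or 60%
- b, share of the other patients who die before the scan: 10% or 20%
- every survivor is scanned and every non-fatal rebleed is seen

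Observed risk among scanned patients = r(1−f) / [r(1−f) + (1−r)(1−b)].

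Example with f = 60%, b = 10%:

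- r = 15%: 0.060 / (0.060 + 0.765) = 7.3%
- r = 5%: 0.020 / (0.020 + 0.855) = 2.3%
- The true 10-point difference is seen as 5.0 points.

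Patients without a value = 120 × the sum over the three arms of [r f + (1−r) b], with both herbal arms at the higher risk. The composite of rebleeding or any death before the scan has risk r + (1−r)b. Power is for one herbal arm against placebo, two-sided 0.05. The scan-only column uses the mean number scanned per arm; the composite uses 120 per arm.

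| True risks | f | b | Observed risks | Difference (points) | Risk ratio | No value, of 360 | Power, scan only | Power, composite with any death |
|---|---|---|---|---|---|---|---|---|
| 15% vs 5% | 40% | 10% | 10.5% vs 3.4% | 7.1 | 3.11 | 49 | 0.53 | 0.43 |
| 15% vs 5% | 40% | 20% | 11.7% vs 3.8% | 7.9 | 3.08 | 80 | 0.52 | 0.28 |
| 15% vs 5% | 60% | 10% | 7.3% vs 2.3% | 5.0 | 3.18 | 57 | 0.39 | 0.43 |
| 15% vs 5% | 60% | 20% | 8.1% vs 2.6% | 5.5 | 3.16 | 89 | 0.38 | 0.28 |
| 10% vs 5% | 40% | 10% | 6.9% vs 3.4% | 3.5 | 2.03 | 45 | 0.21 | 0.15 |
| 10% vs 5% | 40% | 20% | 7.7% vs 3.8% | 3.9 | 2.03 | 78 | 0.21 | 0.10 |
| 10% vs 5% | 60% | 10% | 4.7% vs 2.3% | 2.4 | 2.06 | 51 | 0.16 | 0.15 |
| 10% vs 5% | 60% | 20% | 5.3% vs 2.6% | 2.7 | 2.05 | 84 | 0.16 | 0.10 |

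With every rebleed counted over 120 per arm, power is about 0.74 for 15% vs 5% and 0.31 for 10% vs 5%.

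**Two boundary cases.**

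- If f = b, the survival factor cancels, the observed risk equals r, and there is no bias.
- If rebleeds are more often fatal in the causing arm (f = 70% vs 30%, b = 5%), a true 10% is seen as 0.030 / 0.885 = 3.4% and a true 5% as 0.035 / 0.9375 = 3.7%. The excess disappears.

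**The case against.** The strongest reply is that an article need not say how deaths are scored for one secondary imaging outcome, and that it nowhere states that the rate is taken among scanned patients. That would settle the matter if the article were silent on deaths and missing data. It is not: it sets out its rules, and their limits leave this outcome out. It is fair, though, that the definition does not expressly rule out an unscheduled CT.

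Other parts of the reply stand:

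- **The deaths are not lost to the trial.** All-cause death at day 14, which matches the end of the scan window, is a secondary outcome. Serious adverse events are a safety outcome, recorded to day 90 and validated by an independent committee. What is missing is identification as rebleeding: all-cause death does not show it, and the committee's relatedness categories do not name it.
- **The effect is not confined to one arm.** A reader might infer that the definition understates rebleeding selectively in the arm that causes it. With equal case fatality every arm is understated in nearly the same proportion and the risk ratio holds (3.08 to 3.18 against 3.0). Only differential case fatality hides the contrast, and the article gives no evidence of that.
- **The inputs are assumed.** The 40% figure is 30-day mortality in ICH generally, while this trial requires GCS of at least 6. The time-window justification says enlargement after 24 h is rare, which argues against high late rebleed rates, although it does not describe patients on these herbs. Most of the 45 to 89 patients without a value are assumed other-cause deaths.
- **Intention to treat.** A reader might also see a breach of the stated principle. A missing outcome value is not in itself a departure from analysing patients as randomised.

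**Conclusion.** The point holds as a minor one. The definition and the stated rules together leave fatal rebleeds before the day-10 scan uncounted as recurrent bleeding in all three arms. The article does not support a claim that they vanish from the trial, or that the relative comparison is biased towards no effect.

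The size depends wholly on assumed rates and on rebleeders dying before the scan more often than others. Under the ranges shown, a true 10-point excess is seen as 5.0 to 7.9 points, so 21% to 50% of it is lost, and power falls from about 0.74 to between 0.38 and 0.53. A true 5-point excess is seen as 2.4 to 3.9 points. The severity is minor because the outcome is secondary and the deaths are reported elsewhere.

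**What to change.** In Secondary outcomes, define recurrent bleeding over all randomised patients as either:

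- recurrent bleeding on any CT after the 24-h scan up to the day-10 scan, or
- death before the day-10 scan that the existing clinical events committee, blinded to arm, attributes to rebleeding.

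Treat other deaths before the scan as a competing event and report them by arm. Under the assumptions above this recovers up to the full 10-point difference and power of about 0.74, reached only if every fatal rebleed is identified.

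Give the composite of recurrent bleeding or any death before the scan only as a supporting analysis. Other-cause deaths dilute it: its power is below that of the scan-only definition in 7 of the 8 scenarios, though only just in one of them, and its risk ratio for a true 15% vs 5% is 1.33 to 1.62 (32.0% vs 24.0%; 23.5% vs 14.5%).

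The cost is a change of wording and one added cause-of-death attribution. Deaths and serious adverse events are already recorded and go to the committee, but the article calls it independent of the centres and does not state that it is blinded, so blinding should be specified. The article reports 280 patients already recruited, so earlier deaths would need the same attribution, and the change should be made before the code is broken. Some fatal rebleeds without imaging may be misclassified.

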### Blinding

Before the code is broken following receipt of e-mail notification of the completion of the study, the persons involved in the research including the investigators, subjects and the data analysts are blinded to the interventions and outcomes. Only the data administrators are permitted access to unblinded data.

## Statistical considerations

### Sample size

The primary efficacy outcome is the percent change in the volume of hematoma at the 24th hour after onset in the two treatment groups as compared with the placebo group, assessed via the blinded measurement of hematoma by ABC/2 Coniglobus formula. The statistical hypothesis on the percentage of hematoma expansion is that the relative hematoma volume in subjects of three groups are the same to each other. Power and sample size are determined using relative hematoma volume at 24 h as the main outcome variable. According to the previous literature (Huang et al. 2010; Wang et al. 2013; He et al. 2002), the true proportions of subjects in 3 groups with different rations of hematoma expansion at 24 h are presented in Table 4. In this case, the $$\upgamma$$ is 12.65, $$\uppi\_\hbox{max}$$ 38 % and $$\uppi\_\hbox{min}$$ 7 %. With a two-sided alpha level at 0.05, 285 participants finishing the final follow up provide 90 % power to test the hypothesis of the study’s primary effectiveness, which is calculated by the following formula; assuming that the non-investigation rate of the primary outcomes is 20 %, 360 participants will be needed.

**Table 4 Tab4:** Hypothesized true outcomes for sample size calculations

Randomized group	PBC	RBS	Placebo
Percentage of change	7	16	38

*RBS* removing blood stasis, *PBC* promoting blood circulation

$$n = 1641.6\upgamma/((\sin^{ \wedge } ( - 1)\surd (\uppi\_\hbox{max} )) - \sin^{ \wedge } ( - 1)\surd\uppi\_{\rm min}^{ \wedge } 2$$

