**Conclusions:**

The CRRICH Trial is expected to confirm the safety and effect of acute intracerebral hemorrhage treated within 6 h of ictus with “RBS” therapy and to determine whether the traditional therapy can cause hematoma growth after intracerebral hemorrhage.

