## Study design and methods

### Objective

 The aim of this study is to evaluate the safety and effect of acute intracerebral hemorrhage (AICH) treated with “RBS” therapy and to determine whether the traditional therapy can cause hematoma growth after intracerebral hemorrhage.

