### Data and safety monitoring

The Data Safty Monitoring Committee deliberates the data from intermediate safety analysis report and contacts the Trial Steering Committee. Interim results are extremely secret and once one of the three groups shows a distinct advantage over others, the committee will counsel to end the study ahead of schedule.

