## Discussion

Further prospective, multicenter, randomized, placebo control clinical trials are needed to provide better quality evidence, though in a retrospective study (Xu et al. 2015), we found that PBC and RBS herbal medicine were not associated with an increased risk of hematoma growth within 24 h after the onset of symptoms. Meanwhile, a meta-analysis (Li et al. 2015) which included 9 randomized-controlled clinical trials with 798 individuals showed that PBC and RBS single therapy and combination therapy for acute ICH could reduce the volumes of brain hematoma and cerebral edema, improve the neural function and reduce the mortality and disability rate. Moreover, unlike western conventional medication group, fewer adverse reactions occurred in herb medicine group. In spite of the obviously positive results, It’s too early to draw conclusion about the efficacy and safety of PBC & RBS for ICH since the limitation of the included studies in the meta-analysis. Therefore, high-quality RCTs are needed.

The CRRICH Trial will provide definitive information on the efficacy and safety of the RBS therapy. The trial is designed to learn lessons from study of earlier conservative therapies that cannot demonstrate the treatment benefit of TCM with RBS rather well. Unlike those prior studies (Fan and Jin 2000), the trial set three groups (PBS & RPS & Placebo), better observating the efficacy of RBS or PBS to confirm whether PBC and RBS herbal medicine induce the incidence of hematoma enlargement of AICH patients within the 6 h time window from onset. The shortages of prior studies are as follows: (1) most studies are retrospective, unblinded trials; (2) mixed PBS with RBS; (3) time window from onset is 24 h or later; (4) not multicenter RCT. In order to make up for these limitations, we have designed a prospective, 13 hospitals, randomized, placebo-controlled clinical trial (clinicaltrials.gov: NCT01918722) to confirm if PBC and RBS herbal medicine induce the incidence of hematoma enlargement of AICH patient within the 6 h time window from onset. The trial enrolled its first patient on October 25, 2013. And 280 cases have recruited so far. The study is still ongoing until all 360 patients are completed in December 2016. When completed, we will provide pivotal data allowing.

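### The trial promises an answer on whether the herbs cause haematoma growth, but its equality hypothesis and benefit-based sample size cannot turn a non-significant result into a safety conclusion

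*Protocol article*

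**What the plan says.** The protocol article poses a question about harm. The Objective is "to determine whether the traditional therapy can cause hematoma growth after intracerebral hemorrhage", and the Discussion says the trial is meant to "confirm if PBC and RBS herbal medicine induce the incidence of hematoma enlargement". The abstract's Conclusions paragraph says that the trial "is expected to confirm the safety and effect of acute intracerebral hemorrhage treated within 6 h of ictus". Under Secondary outcomes, growth is listed on the safety side: "Two study safety outcomes are included as follows: (1) all serious adverse events; (2)hematoma growth at 24 ± 3 h".

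The statistics point towards benefit. The Sample size section calls the endpoint an efficacy outcome and states one hypothesis, that "the relative hematoma volume in subjects of three groups are the same to each other". It adds that "the true proportions of subjects in 3 groups with different rations of hematoma expansion at 24 h are presented in Table 4": PBC 7, RBS 16, placebo 38. From these it derives 285 evaluable participants, 90% power at two-sided 0.05, and 360 randomized after 20% loss.

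The Statistical analyses section names an alpha of 0.025, a threshold of 0.0167 for each herbal arm against placebo, and 0.05 for all other comparisons. The primary analysis is a mixed model on log-transformed percent change.

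On early stopping, Data and safety monitoring says that "once one of the three groups shows a distinct advantage over others, the committee will counsel to end the study ahead of schedule".

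**The concern.** A test of equality answers the harm question in one direction only. If it rejects with the herbal arm worse, harm is shown. If it does not reject, the result is compatible with no effect and with every harm inside the confidence interval. The article gives no harm hypothesis and no largest increase to be ruled out, so nothing connects a null result to the conclusion that safety is confirmed.

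The sample size makes this matter in practice. It was chosen to find benefits of 22 points (38 − 16) and 31 points (38 − 7). A trial of that size may be unable to exclude a much smaller harm, yet a smaller harm could still matter for drugs given within 6 h of a bleed. The article itself names rebleeding as a risk of one ingredient type.

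**Working it through.** **Inputs.** From the article: growth rates of 38%, 16% and 7% (Table 4); 285 evaluable at 1:1:1, so 95 per arm; 360 randomized, so 120 per arm; thresholds 0.05, 0.025 and 0.0167. My assumption: a harm of 10 to 12 points, because the article gives no harm of concern. Scale: the proportion with >33% growth, which is how the article defines growth and the scale of its sizing formula.

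**The plan's own figure.** The arcsine formula, in degrees with γ = 12.65, gives:
- 38% and 7%: 1641.6 × 12.65 / (38.06 − 15.34)² = 40.2, so 41 per arm and 123 in all.
- 38% and 16%: 1641.6 × 12.65 / (38.06 − 23.58)² = 99.1, so 100 per arm and 300 in all.

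Neither gives 285, so that figure is not reproduced. This is a separate matter. The step from 285 to 360 is consistent with 20% loss (285 / 0.8 = 356.25). I take 95 and 120 per arm as given.

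**Power for the assumed benefits, 95 per arm.** 38% against 7%: over 99% at every threshold. 38% against 16%: 93% at 0.05 and 85% at 0.0167.

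**Power for harm.** Two-sided test of two proportions with pooled variance under the null:

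power = Φ[(d − z·SE₀) / SE₁], with SE₀ = √(2p̄(1 − p̄)/n) and SE₁ = √((p₁(1 − p₁) + p₂(1 − p₂))/n).

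For 38% against 48% with n = 95: p̄ = 0.43, SE₀ = 0.0718, SE₁ = 0.0715.
- At 0.05: Φ[(0.10 − 1.96 × 0.0718)/0.0715] = Φ(−0.57) = 28%.
- At 0.0167: Φ[(0.10 − 2.393 × 0.0718)/0.0715] = Φ(−1.01) = 16%.

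| Placebo 38% | α = 0.05 | α = 0.025 | α = 0.0167 |
|---|---|---|---|
| +10 points, 95 per arm | 28% | 20% | 16% |
| +12 points, 95 per arm | 38% | 28% | 23% |
| +10 points, 120 per arm | 35% | 25% | 20% |
| +12 points, 120 per arm | 47% | 36% | 30% |

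With 95 per arm, 80% power needs a rise of about 20 points (0.05) or 23 points (0.0167).

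**Sensitivity to the placebo rate, 95 per arm, thresholds 0.0167 to 0.05.** At 20%: 21% to 36% for +10 and 30% to 47% for +12. At 10%: 32% to 49% for +10 and 45% to 62% for +12.

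**What a perfectly null result would exclude.** With 38% in both arms, SE = √(2 × 0.38 × 0.62/95) = 7.04 points. The half-widths are:
- 95% interval: 1.96 × 7.04 = 13.8 points
- 97.5% interval: 2.241 × 7.04 = 15.8 points
- 98.33% interval (matching 0.0167): 2.393 × 7.04 = 16.9 points

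An observed difference of zero would therefore not exclude a 10 to 12 point increase. For scale, ruling out such an increase with 80% power at one-sided 0.025 and equal rates of 38% would need 370 per arm (10 points) or 257 per arm (12 points).

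**The case against.** - **The planned analysis is not a two-proportion test.** It is a covariate-adjusted mixed model on log-transformed percent change. This stands: no SD is given, so power in that model cannot be computed, and it may be higher. The figures above describe the >33% scale only.
- **The choice of threshold and n matters.** Haematoma growth as a safety outcome arguably falls under the 0.05 rule, and intention to treat with imputation argues for 120 per arm. A reader might infer from 0.0167 and 95 per arm that 77% to 84% of such harms would be missed. That is the pessimistic end of the range and should not be quoted alone. At 38% on placebo, power is below 50% at every combination in the table.
- **Two-sided tests can show harm.** True, and large harms of about 20 to 23 points would usually be found. The gap is moderate harm, and any safety claim drawn from non-significance.
- **Nobody says that a null result means safe.** A reader might infer it from the abstract's Conclusions and the Discussion, but no decision rule in the article states it. What stands is that the article promises to confirm safety and gives no other route to that conclusion.
- **This is a condensed article.** Confidence intervals are commonly left to the analysis plan, so their absence alone is no defect. The mismatch between the stated question and the stated hypothesis and sizing is on the page.
- **Monitoring.** A reader might infer that the committee acts only on an advantage. The text does not say only: the committee reviews an interim safety report, and placebo doing better than both herbal arms would meet the condition. The remaining gap is narrow: one herbal arm worse than two similar arms does not fit the only stopping condition written down.

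**Conclusion.** The concern holds in a limited form. The article makes haematoma growth from the herbs a headline question and expects to confirm safety, but it states only an equality hypothesis and is sized on benefits of 22 to 31 points. A non-significant result cannot support a safety conclusion.

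The size of the gap rests on two assumptions: the binary >33% scale with the article's own 38% on placebo, and a 10 to 12 point harm that the article does not name. With 95 per arm, power is then 16% to 38%; with 120 per arm, 20% to 47%. At placebo rates well below 38% the gap narrows, and at 10% the power for +12 points can pass 50%.

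The superiority comparisons are not invalidated, and the documents do not show that the trial is blind to harm. The defect lies in what may be concluded from a null result, and it can be repaired cheaply. It should be fixed, but it is not fatal.

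**What to change.** 1. Keep the two-sided superiority tests.
2. For each herbal arm against placebo, report the difference in the proportion with >33% growth, with a confidence interval at the level that matches the chosen multiplicity threshold. The article names 0.05, 0.025 and 0.0167, so the choice must be stated.
3. Before unblinding, fix the largest increase to be ruled out. Claim that an herbal arm does not cause haematoma growth only if the upper limit lies below it. Otherwise report the largest increase not excluded.
4. Reword the abstract's Conclusions and the Discussion to match, and state the expected half-width of about 14 to 17 points (13.8 to 16.9 above) beside the aim.
5. Separately, reconcile the early-stopping sentence in Data and safety monitoring with the trial's safety aim.

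Cost: wording and one interval per comparison, with no extra patients. The Blinding section keeps the code closed until completion, so the margin can still be set blind. The attainable safety claim becomes more modest. With equal rates of 38%, 95 per arm and a 97.5% interval, an 80% chance of success needs a margin of (2.241 + 0.842) × 7.04 = 21.7, or about 22 points. A margin of 16 points would succeed only about half the time.

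### With its stated inputs the sample-size formula gives 41 per group (123 in all), not 285, and the 90% power is unsupported for the planned primary analysis

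*Protocol article*

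**What the plan says.** The Sample size section of the protocol article begins its power claim with these words: "With a two-sided alpha level at 0.05, 285 participants finishing the final follow up provide". The power claimed is 90%, and the section attributes the number to an arcsine formula that it prints. Its inputs are γ = 12.65, π_max = 38% and π_min = 7%. It then allows 20% for missing primary outcomes and arrives at 360.

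The null hypothesis there is that "the relative hematoma volume in subjects of three groups are the same to each other". The text introduces Table 4 as giving "the true proportions of subjects in 3 groups with different rations of hematoma expansion at 24 h", but the table's own row reads "Percentage of change 7 16 38" for PBC, RBS and placebo.

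The Primary outcome section makes the endpoint the percent change in hematoma volume at 24 h, which is continuous. Under Statistical analyses, "The volumes of the hematoma measured by a CT scan will be analyzed using generalized linear mixed models". Percent changes are log-transformed, and each of the two herbal groups is compared with placebo at a Bonferroni threshold of 0.0167. The same section opens with an alpha of 0.025 and a beta of 0.10.

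**The concern.** There are two separate problems in one paragraph.

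First, the article attributes 285 to a printed formula and gives every input, but the formula does not return that number, so a reader cannot tell which of the inputs or the result is in error.

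Second, the formula belongs to a different test from the one planned. It concerns proportions, all three groups at once, at 0.05. The plan analyses a continuous variable, in pairs against placebo, at a stricter threshold. The 90% therefore does not describe the analysis on which the trial will report. At stake is whether each herbal arm's comparison with placebo has the sensitivity claimed, which matters in particular if a comparison turns out not to be significant.

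**Working it through.** **Inputs.** From Sample size and Table 4: γ = 12.65; PBC 7%, RBS 16%, placebo 38%; alpha 0.05; power 90%; 20% loss. From Randomization: 1:1:1, so 285 is 95 per group. From Statistical analyses: thresholds 0.0167 and 0.025.

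**1. Which test the formula sizes.** The chi-square noncentrality for 2 df, alpha 0.05 and power 0.90 is 12.654, which matches the stated γ. The formula is therefore the arcsine formula (in degrees) for an overall comparison of three proportions:

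n per group = 1641.6 γ / (arcsin√π_max − arcsin√π_min)²

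**2. The plan's own figure.**
- arcsin√0.38 = 38.057°, arcsin√0.07 = 15.342°, difference 22.715°.
- n = 1641.6 × 12.65 / 22.715² = 20766 / 515.97 = 40.25, so 41 per group and 123 in all.
- The radian form, γ/(2d²), gives 40.24 per group. A three-group Pearson chi-square using all three rates gives a total of 121.

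The stated 285 is 285/123 = 2.3 times the formula's result.

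**3. Whether the broken brackets explain it.** The printed formula has unbalanced brackets, so other readings were tried with the same inputs:
- difference not squared: 914
- π_min squared and difference not squared: 20766 / (38.057 − 4.014) = 610
- π_min squared and difference squared: 17.9
- square applied to the second arcsine only: negative

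None gives 95 or 285.

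**4. Whether another input explains it.** With π_min = 16% (RBS), the difference is 14.479° and n = 99.06, or 297 to 300 in all. Exactly 95 per group needs π_min of about 15.6%. A continuity-corrected two-proportion test of 38% against 16% at 0.05 gives 93 per group (279 in all), but that contradicts the stated formula, γ and π_min.

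**5. Power of the sized test at 285.** Noncentrality is 95 × 515.97 / 1641.6 = 29.86 on 2 df, so power at 0.05 is about 99.9%. At 41 per group it is 90.5%.

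**6. The loss step.** 285 / 0.8 = 356.25, so 357. The stated 360 is an acceptable rounding.

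**7. Pairwise power, as a proxy only.** Assume Table 4 holds proportions of patients, and use an unadjusted two-sided comparison with 95 per arm:

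power = Φ{(|p₁ − p₂|√n − z√(2p̄q̄)) / √(p₁q₁ + p₂q₂)}

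For RBS against placebo at 0.0167: (0.22 × 9.747 − 2.393 × 0.628) / 0.608 = 1.055, giving 85.4%.

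| Contrast | at 0.0167 | at 0.025 |
|---|---|---|
| PBC vs placebo (7% vs 38%) | 99.8% | 99.9% |
| RBS vs placebo (16% vs 38%) | 85.4% | 88.7% |

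**8. The planned analysis.** No mean, ratio or SD of the volume change is given, so its power cannot be computed. What can be computed is the assumption that 90% would need. With 1-df noncentrality 13.504 (0.0167) or 12.411 (0.025), a simple two-arm comparison with 95 per arm requires a difference of √(2 × 13.504/95) = 0.53 SD or √(2 × 12.411/95) = 0.51 SD on the log scale, before any gain from covariates. The article does not say whether a difference of that size is expected.

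**The case against.** The strongest defence is that the number of patients is not shown to be inadequate. For the test the formula sizes, 285 is generous, and 360 need not change. On the proxy, RBS against placebo would have about 93% power at 0.0167 if all 120 per arm were evaluable. This stands: the finding concerns what the paragraph claims, not a shortfall in enrolment.

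Four stronger readings are tempting, and the documents do not support them.

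- *That 41 per group is the correct requirement.* It is what the stated inputs give, but π_min may be the misstated item. The RBS rate gives 99 to 100 per group, and 300 × 1.2 is 360. That is an inference, because the article does state 7% and neither 297 nor 300 is 285. Writing 41 into the protocol could replace one error with another.
- *That 90% is too high for RBS against placebo in the planned analysis.* The 85% comes from an unadjusted comparison of proportions, which is not the planned test. Without an SD, the planned contrast could have more or less than 90%.
- *That Table 4 gives rates of growth above 33%.* The CT scanning and Primary outcome sections define growth by that cut-off, but the Sample size section attaches none to Table 4.
- *That growth above 33% should become the primary endpoint to match the formula.* The Discussion reports 280 of 360 patients already recruited. At that stage this would be a major amendment, not a correction of text.

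**Conclusion.** The statement linking 285 evaluable participants to 90% power is wrong as written. The stated inputs give 123 in all, and 285 would give about 99.9% for the test named. This part rests only on figures in the article and does not depend on how the broken brackets are read.

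The 90% is also unsupported for the planned primary analysis, because that analysis uses a different variable, different comparisons and a different threshold, and its assumptions are not stated. It is not shown to be too high or too low. The proxy figures of 99.8% and 85% (89% at 0.025) assume that Table 4 holds proportions and that 95 per arm are evaluable. They show only that one figure of 90% would not fit both contrasts.

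**What to change.** Keep 360 and the continuous primary endpoint, and revise the Sample size section as follows:

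1. Correct the printed formula, and reconcile π_min, n per group and N so that the formula reproduces the stated number.
2. Say whether Table 4 gives proportions of patients, and at what cut-off, or mean percent changes.
3. Use one alpha scheme in both sections. At present 0.05, 0.025 and 0.0167 all appear. Since 0.05/2 = 0.025 and 0.05/3 = 0.0167, state how many comparisons the adjustment covers.
4. Restate power for each herbal arm against placebo at the threshold actually used, from an assumed ratio and SD of log(V24/V0), where V24 and V0 are the 24 h and baseline volumes, with the source of each.
5. If Table 4 does hold proportions, its pairwise figures may be added as supporting information, labelled as such.

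The cost is text in the sample-size section, with alpha in Statistical analyses brought into line. Enrolment does not change, and one stated power may become slightly less favourable.
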